
#### Intervention B—Melatonin supplement group

Participants in this intervention group will undergo a 10-week melatonin supplement intervention period, where melatonin supplement (Natrol®, Chatsworth CA) will be provided 30 minutes before bedtime [19]. The prescription time (i.e. 30 minutes before bedtime) and the dosage of 3mg will be used because these are optimal for most of the participants as suggested by Malow and colleagues [19]. 1 mg and 9 mg are not suggested to ensure the effectiveness of the intervention while preventing the potential daytime sleepiness. Similar to the aforementioned intervention, adherence of the intervention will be assessed at T2.

#### Intervention C—Combination group

Participants will receive the jogging program and supplemental melatonin dose with identical format as that in the intervention A and B (e.g., identical duration, identical manpower, identical warm-up and cool-down, identical dose, identical acclimation procedure before the intervention adherence of the intervention for this group will also be assessed at T2.

#### Placebo control group

Participants in the control group will receive no jogging and melatonin supplement dosing activity. However, they will be given a placebo flavored similar to the melatonin supplement (compounded by Pharmacare, Mt. Juliet, NT®). Meanwhile, they will also be required to wear an actigraph to control for their physical activity level at the assessment points (i.e. T1, T2, and T3). They will be expected for following their daily routine without participating in any additional formal physical exercise training program throughout the whole study period (T1-T3). After T3, they will be assisted with jogging program to recognize their contribution as controls.

To ensure all the interventions are delivered as intended, regular meetings among the research team will be hosted by the PA to monitor the progress and to discuss any difficulty encountered. Meanwhile, each participating family will be provided with a financial incentive, which is a good strategy evidenced by a high compliance rate in our ongoing study.

### Study measures

The demography and developmental history of each participant will be obtained from their parents or schools. And the following measurements will be carried out at T1, T2 and T3.

#### Primary outcome measures

*Sleep*. Four sleep parameters including sleep onset latency (length of time taken to fall asleep, expressed in minutes, SOL); sleep efficiency (actual sleep time divided by time in bed, expressed as a percent, SE); wake after sleep onset (length of time they were awake after sleep onset, expressed in minutes, WASO) and sleep duration (total sleep in hours and minutes, SD) will be objectively measured by a GT3X accelerometer [19]. Participants will be asked to wear the device on the non-dominant wrist for seven consecutive days (Monday to Sunday). Non-wear time is defined as 60 min of consecutive zeros with a 2-min spike tolerance [19, 20]. The night (2200–0700) will be considered invalid if the wear time is less than 8 h and will be excluded from the analysis. In addition, participants’ sleep patterns will be logged by their parents using Children’s Sleep Habits Questionnaire–Chinese version (CSHQ-C) [21], which is a validated 45-item parent-administered questionnaire to examine sleep patterns of young children including children with ASD [21]. Moreover, parents will be also asked to log the bedtime, sleep latency, sleep start, sleep end, wake-up time and assumed sleep length in a sleep log for the whole assessment week.

*Endogenous melatonin level*. The endogenous melatonin level of the participants, reflected by the 6-sulfatoxymelatonin (aMT6s, creatinine-adjusted morning urinary melatonin representative), will be measured from their 24-h and first morning urinary samples during weekend and Monday respectively [14], and the participants will be required to stay at home for sample collection. All urine samples will be collected using 24-h and first morning void urine bottles. Once they have been collected, the research staff will immediately collect the samples and they will be stored at −80°C before analysis.

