**Methods:**

All eligible participants will be randomly allocated to a morning jogging group, a melatonin supplement group, a combination group and a control group. Changes in sleep quality will be monitored through actigraphic assessment and parental sleep logs. Melatonin levels represented by 6-sulfoxymelatonin will be measured from the participants’ 24-h and the first morning void urinary samples. All the assessments will be carried out before the intervention (T1), in the mid of the study (5 weeks after the commencement of the study) (T2) and after the 10-week intervention (T3). Level of statistical significance will be set at 5% (i.e. *p* < .05). The results of this trial will be submitted for publication in peer-reviewed journal.

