### Participants

Participants will be screened using the following inclusion criteria: (1) clinical diagnosis of ASD by a physician based on the Diagnostic and Statistical Manual of Mental Disorders, 5th edition, (DSM-5) [15]; (2) age 8–11 years; (3) pre-puberty as indicated by Tanner stage I through screening by a physician (to prevent any puberty influence on hormonal response); (4) being given an average of 8 hours of sleep per night by their parents over the past 3 months; (5) parents reported sleep onset delays of 30 minutes of longer on three or more nights per week; (6) free of psychotropic medications (allergy medications and medications for constipation are allowed); (7) non-verbal IQ over 50 using a brief version of Wechsler intelligence scale for children (Chinese revised, C-WISC) [16] (since lower IQ is liked to higher prevalence of comorbid psychiatric disorders and seizures); (8) Social Response Scale T-score 80 or above (to control for the ASD severity) and (9) no concurrent medication for at least three months before the study or any prior melatonin treatment.

Exclusion criteria are: (1) with one or co-morbid psychiatric disorders; (2) with other medical conditions that limit their physical exercise participation and sleep (e.g., asthma, seizure, cardiac disease etc); and (3) with a complex neurologic disorder (e.g., epilepsy, phenylketonuria, fragile X syndrome, tuberous sclerosis) and (4) participants who are currently meeting physical exercise guidelines (i.e. 60 minutes of moderate and vigorous physical exercise each day).

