### Sample size calculation

Previous study [13, 14] showed physical exercise had notable effects (corresponding to a Cohen’s *d* of about 0.9) on improving sleep onset latency, sleep duration and sleep duration. We assumed that melatonin supplements have similar effects on sleep. A sample of 20 participants per group is computed by G*power software to achieve a power of 80% and a level of significance of 5% and 95% confidence level. Assuming 25% attrition rate, 25 participants per group will be recruited (i.e. the total number is 100).

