### Statistical methods

All statistical analyses will be conducted using SPSS (version 26.0) for Windows (SPSS Inc., Chicago, IL, USA). All the data will be entered into SPSS by the research assistant. One-way (4 Groups: physical exercise vs melatonin supplement vs combined exercise and melatonin supplement vs placebo-control) analysis of variances (ANOVA) with repeated measures will be performed to compare changes in actigraphy data and endogenous melatonin level between and within groups over different time points (i.e. T1-T3). Post-hoc analyses will be performed when any significant difference both between- and within-group is found in any of the outcome variables. Bonferroni correction will be used to adjust the alpha levels. Depending on the proportion of missing data and the assumption of normality, multilevel regression or a generalized estimating equation (GEE) will also be used as a sensitive analysis to assess the effects of the physical exercise intervention, melatonin supplement, time effect, and their interaction with sleep outcomes and melatonin level outcomes if there is any missing data. Average time spent in both daily sedentary activity and MVPA at baseline will be used as covariates. Linear regression will be used to analyse the association between participant’s adherence to the intervention and the outcome variables as a secondary analysis. Mediation analysis will be conducted to examine the mediating effect of endogenous melatonin level at T2 on the relation between physical exercise and sleep at T3. Preacher and Hayes’ bootstrapping and conditional process modeling will be used to determine the significance of the mediating effect. A p-value of <0.05 will be considered statistically significant. Both proposal analysis and intention-to-treat analysis will be carried out. Demographic variables (e.g. age, sex, BMI) will be adjusted if they demonstrate clinically significant prognostic effects on the outcomes (with absolute correlation or Cohen’s d effect size of >0.2) for both main analysis and mediation analysis.

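### Four unranked primary sleep parameters, each tested at 0.05 with an any-outcome trigger, push the false-positive rate above 5% and leave the most effective intervention undefined

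*Protocol article*

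**What the plan says.** All references are to the protocol article.

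- **Primary outcome measures** lists "Four sleep parameters including sleep onset latency" together with sleep efficiency, wake after sleep onset and sleep duration, all by actigraphy. The CSHQ-C and a parent sleep log stand under the same heading. So does aMT6s, which "will be measured from their 24-h and first morning urinary samples". No order or lead measure is given. Only physical activity is listed as secondary.
- **Introduction**: the first objective is to find which intervention does more for sleep quality, tied to no one measure or time point. The melatonin mechanism is a separate, second objective.
- **Statistical methods** applies a four-group repeated-measures ANOVA to the actigraphy data and the melatonin level over T1 to T3. It then says: "Post-hoc analyses will be performed when any significant difference both between- and within-group is found in any of the outcome variables". The next sentence promises a Bonferroni correction without saying over which tests. Later: "A p-value of <0.05 will be considered statistically significant".
- **Sample size calculation**: "A sample of 20 participants per group is computed by G*power software". The target is 80% power at a 5% level, with d of about 0.9. No division of the 5% is mentioned.

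**The concern.** The primary set and the rule for opening comparisons are both stated, and together they do not hold the 5% level. Any of four sleep parameters may open the group comparisons, and nothing in the text adjusts for there being four. A false lead on one parameter can therefore become the trial's answer.

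The second problem remains even with perfect error control. If jogging leads on sleep efficiency and melatonin on sleep onset latency, the plan does not say which result settles the first objective.

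**Working it through.** **Inputs.** Level 0.05 (Statistical methods). d = 0.9, 20 analysed per group, power 80% (Sample size calculation). Four groups, equal allocation (Study design in the abstract). Four actigraphic parameters (Primary outcome measures). Assumed because the article does not state them: two-sided tests, and a common correlation between parameters, shown over a range.

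**1. The plan's own figure.** n per group = 2(z₀.₉₇₅ + z₀.₈₀)²/d² = 2(1.960 + 0.842)²/0.81 = 19.4, so 20. This matches. The exact t-test gives 21, with 79.2% power at n = 20. A one-sided test would give 16. So 20 per group corresponds to one two-group comparison on one outcome at an undivided two-sided 0.05.

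**2. False omnibus result on at least one of four sleep parameters.** If independent: 1 − 0.95⁴ = 0.185. For correlated parameters, one-way F tests were simulated under the null with four groups of 20 (one group test per parameter, a simplification of the repeated-measures model):

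| Correlation | 0 | 0.3 | 0.5 | 0.7 | 0.9 |
|---|---|---|---|---|---|
| At least one false omnibus | 18.5% | 17.5% | 16.0% | 13.7% | 9.8% |

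**3. False pairwise claim after the full chain.** An omnibus p < 0.05 on a parameter was required, then at least one of its six group pairs significant at 0.05/6. Under the null, the chance of this on at least one of the four parameters is about 15% at correlation 0, 13% at 0.5 and 11% at 0.7.

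**4. If Bonferroni was meant to span the four outcomes.** The level is 0.05/4 = 0.0125. With noncentrality 0.9·√(20/2) = 2.85 on 38 degrees of freedom, exact power at n = 20 is 59%. To regain 80%: 2(2.498 + 0.842)²/0.81 = 27.5, so 28 per group (30 by the exact t-test).

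**5. If one primary outcome is kept and Bonferroni runs over its six pairs.** The level is 0.05/6 = 0.0083. Exact power at n = 20 is 53%.

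**The case against.** The strongest reply is that Bonferroni is promised and that an unseen analysis plan may define its family. An omnibus result is also not yet a declared winner, because adjusted post-hoc tests follow. Part of this stands: counting the post-hoc step lowers the error from 14–19% to 11–15% over correlations 0.7 to 0. That is still at least twice 5%. Extending Bonferroni to the outcomes would control the error but contradict the sample size, which rests on an undivided 5%. Neither reading ranks the outcomes.

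A reader might also infer more than the article supports:

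- **A rate of 30.2% (1 − 0.95⁷), counting the CSHQ-C.** The ANOVA sentence names only actigraphy and melatonin. No CSHQ-C test is specified.
- **A rate of 26.5% (1 − 0.95⁶), counting both aMT6s measures.** These serve the mechanism objective and do not say which intervention improves sleep more.
- **Virtually no power if everything is adjusted.** Four outcomes by six pairs (0.05/24) leaves 34% at d = 0.9 and n = 20. That is far below 80% but not negligible, and the article specifies no such family.
- **A main time effect as a required gate.** The phrase about between- and within-group differences can mean differences of either kind, and the group-by-time interaction is itself a within-subject test. The sentence needs clarifying, but the strict reading is not established.
- **Sleep onset latency as the only proper primary.** The sample-size section also cites sleep duration. The Introduction's account of the earlier exercise studies reports gains in sleep efficiency, wake after sleep onset and sleep duration, and none in onset latency.

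**Conclusion.** The point holds for the sleep objective. Followed as written, the plan gives up to 18.5% chance of at least one false omnibus result across the four parameters (about 14 to 16% at correlations 0.7 to 0.5). The chance of at least one false adjusted pairwise claim is about 11 to 15%. If Bonferroni was meant to cover the four outcomes, power is 59% against the stated 80%. On either reading, the parameters can disagree and the plan does not say which one decides.

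These figures assume 20 analysed per group, two-sided tests and equal correlations between parameters. The correlations are assumed, since the article gives none; even at 0.9 the omnibus rate is about 10%. The fault lies in rules the article states, so it is not merely detail left to an analysis plan.

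**What to change.** Choose one of two routes before unblinding.

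1. **One primary.** Name one sleep outcome at T3. Make the other sleep parameters, the CSHQ-C and aMT6s secondary, with aMT6s tied to the mechanism objective. Actigraphic sleep onset latency is one candidate: the sample-size section cites it, and eligibility requires "parents reported sleep onset delays of 30 minutes of longer on three or more nights per week", although that is a parent report. Sleep duration is cited in the sample-size section too. The choice is the sponsor's.
2. **Four primaries.** Keep all four, apply Holm across them, say how conflicting results will be read, and restate the power. Holm's first step is at 0.0125, where power is 59% at n = 20.

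Under either route, base the group comparisons on the between-group (group-by-time) effect rather than a main time effect, and keep Bonferroni or Holm over the pairwise contrasts on each primary outcome.

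**Cost.** Amendment wording; every measure is still collected. With route 1, results on the other sleep parameters become secondary. With route 2, the stated power falls or the sample must grow. Route 1 also needs a plain statement that 20 per group supports about 80% power only for one pairwise contrast at 0.05, and 53% with Bonferroni over all six pairs.

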#### Intervention A—Morning jogging group

The training protocol, assessment and instructional technique will be referenced on our previous protocol in children with ASD [17]. However, we will modify the frequency of the jogging sessions to suit the comparison with other intervention group (i.e. intervention B and C). This intervention will be a 10-week jogging program consisting of 50 sessions (5 sessions per week, 30 min per session) in each participating school. The increase of jogging sessions from the previous protocol [17] is to make the prescription equivalent to the melatonin supplement prescription for other interventions (B and C), which will be prescribed to the participants every day, according to the previous protocol [17]. Moreover, this is more close to the World Health Organization (WHO) recommendation that everyone should participate in physical exercise daily. Meanwhile, the jogging program is confined to morning sessions based on the favourable sleep outcomes from previous study [18]. To counteract the possible influence of natural sunlight exposure, all jogging sessions will be confined to indoor setting. Each intervention session will be administered by a trained research assistant assisted by student helpers. All the research staff (i.e. student helpers and research assistant) will be required to attend a workshop to standardize the procedure on implementing the intervention, as well as handling and motivating their ASD partners. Each session will be conducted in an identical format with 5 minutes of warm-up activities, followed by 20 minutes of jogging (intervention), and 5 minutes of cool-down activities. In the jogging activity, participants will be asked to jog side-by-side with the research staff around an activity circuit (57m x 50m) marked with 4 red cones. Participants are instructed to jog at a moderate intensity level. The intensity level of jogging will be measured by heart rate monitor (Polar H1). Considering the general low physical fitness of children with ASD, physical exercise with a heart rate above 50% of the maximum heart rate (subtracting the participant’s age from 220) is regarded as moderate intensity. Motivation techniques (e.g. verbal cue, visual chart, favourite post-intervention activity) will be used to enhance the compliance rate. Meanwhile, questionnaire will be given to the research staff assisting the jogging intervention to assess the adherence of the intervention at T2. The feasibility, community-viability and sustainability of the exercise intervention are confirmed with previous research experience and the cooperation of the participating schools. Since these intervention sessions are conducted in the morning hours before school start times, the participants may get less sleep time since they must arrive at school early enough to do the exercise. To ensure the participants to have sufficient sleep, they are strongly encouraged to go to bed earlier at night.

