#### Secondary outcome measure

*Physical activity level*. The physical activity level of the participants will also be measured as secondary data to examine its relationship to cognitive functions as suggested by previous studies [22, 23]. It will be measured using accelerometers (i.e. GT3X). The data used for analysis are the times spent in sedentary activity and MVPA based on the default energy expenditure algorithm in the accelerometer device [24]. The day (0700–2100) will be considered invalid if the wear time is less than 10 hours and will then be excluded from the analysis.

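### The night-time wear rule can void a fully worn night because the child lay still for just over an hour, so exclusion depends on the primary sleep outcomes

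*Protocol article*

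**What the plan says.** All of this is in the protocol article, section Study measures.

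- Under Primary outcome measures, sleep onset latency (SOL), sleep efficiency (SE), wake after sleep onset (WASO) and sleep duration "will be objectively measured by a GT3X accelerometer", worn on the non-dominant wrist for a week at each assessment.
- Non-wear has one definition: "Non-wear time is defined as 60 min of consecutive zeros with a 2-min spike tolerance". No separate definition is given for the sleep period.
- Night validity: "The night (2200–0700) will be considered invalid if the wear time is less than 8 h and will be excluded from the analysis".
- Under Secondary outcome measure, the daytime counterpart: "The day (0700–2100) will be considered invalid if the wear time is less than 10 hours".
- A parallel parent record exists: "parents will be also asked to log the bedtime, sleep latency, sleep start, sleep end, wake-up time and assumed sleep length in a sleep log". Nothing says that this log overrides the zero-count rule.

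**The concern.** A run of zero counts cannot by itself separate a device left on the bedside table from a device on the wrist of a soundly sleeping child. By day that ambiguity is minor. At night, prolonged stillness is what the device is there to detect, because actigraphy infers sleep from lack of movement. A rule that voids nights for long stillness therefore selects on the outcome.

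All four primary actigraphy outcomes are computed only on surviving nights. If the survivors are disproportionately restless, SE is understated and WASO overstated. If an intervention makes sleep more consolidated, its arm may lose more follow-up nights than control, and the estimated difference would shrink toward zero. Averaging over the remaining nights of the week does not remove this, because the loss is not random. The trial plans on 20 analysable children per group, so avoidable loss of nights matters.

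**Working it through.** **Step 1. The stated rule, no assumptions.**

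Inputs (Primary outcome measures): window 2200–0700; minimum wear 8 h; non-wear is a zero run of at least 60 min.

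- Window = 9 × 60 = 540 min. Required wear = 8 × 60 = 480 min. Slack = 540 − 480 = 60 min.
- Wear = 540 − (sum of all zero runs of 60 min or more). The night is invalid if wear < 480.

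| Still spells on a fully worn night | Counted wear (min) | Night |
|---|---|---|
| one of 59 min | 540 | valid |
| one of 60 min | 540 − 60 = 480 | valid |
| one of 61 min | 540 − 61 = 479 | invalid |
| one of 90 min | 540 − 90 = 450 | invalid |
| two of 60 min | 540 − 120 = 420 | invalid |

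The slack equals the shortest spell that can be flagged, so one qualifying spell a minute over the threshold is enough. The spike tolerance makes such spells easier to reach.

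**Step 2. Comparison with the daytime rule.** The day runs 0700–2100, which is 14 h, and 10 h are required, so 14 − 10 = 4 h of flagged time is tolerated. The allowance is 1 h at night, when stillness is expected, and 4 h by day.

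**Step 3. How many worn nights could be lost.** The article gives no movement rate, so these are assumptions. In simulated 540-min nights, each minute contains movement independently with a fixed probability, and a night is rejected if flagged minutes exceed 60:

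| Minutes with movement | No spike tolerance | At most 2 non-zero minutes per spell |
|---|---|---|
| 5% | 71% | 100% |
| 10% | 8% | 76% |
| 15% | 0.4% | 17% |
| 20% | 0% | under 1% |

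A third reading of the tolerance allows any number of interruptions of up to 2 min each. It rejects essentially every night even at 30% movement. The article does not say which reading applies.

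A second version has 8 h of sleep, one hour always active and no tolerance. It rejects 93% of worn nights at 2 movement minutes per hour, 67% at 3, 36% at 4, 17% at 5, 7% at 6 and 1% at 8.

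**Step 4. Direction.** Assume nightly SE with mean 80% and SD 7, and let the movement rate fall as SE rises from 70% to 90% (second version of Step 3):

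| Movement minutes per hour at SE 70% → 90% | Nights rejected | Mean SE, rejected | Mean SE, kept |
|---|---|---|---|
| 6 → 2 | 43% | 84.5% | 76.6% |
| 6 → 3 | 31% | 84.6% | 78.0% |
| 8 → 4 | 13% | 87.1% | 78.9% |

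Against a mean of about 80% over all nights, the kept nights read about 1 to 3 points too low. The link between stillness and SE is built into this illustration. It shows the direction and does not estimate the bias in this trial.

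**The case against.** The strongest reply is that nothing here is quantified from the documents. The loss runs from almost none to all nights depending on an assumed movement rate. Eligible children have sleep-onset delays of 30 minutes or longer on several nights a week, so part of the window would be wakeful and a single rate for all 540 minutes is crude. The rule also rests on cited references that may handle sleep data differently and cannot be consulted here. All of this stands as a limit on size. It does not touch the arithmetic of the rule as written, which makes no exception for sleep.

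Four stronger readings are tempting and are not supported.

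- *The rule removes precisely the well-slept nights.* It also removes nights when the device really was off, and it keeps good nights broken by enough small movements. It is a tendency.
- *Sleep is scored only inside 2200–0700, so earlier bedtimes lose sleep.* The article uses that window only to judge validity, and defines SE against time in bed.
- *The rule acts differently in the jogging arms by design.* Joggers are told that "they are strongly encouraged to go to bed earlier at night", but an earlier bedtime does not reduce wear between 2200 and 0700. Nothing says that the device comes off on rising, and the daytime measure uses the same device type from 0700. T1 precedes and T3 follows the programme, so early rising for sessions would overlap assessment mainly at T2. Only a conditional statement survives: an arm that sleeps more stilly may lose more nights.
- *The existing log already settles wear.* Its listed fields do not include device removal.

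**Conclusion.** The concern holds in a limited form. It is certain from the stated figures that one motionless spell of more than 60 minutes, or two of 60, invalidates a night on which the device was worn throughout. Exclusion therefore depends on stillness, the quantity from which the primary outcomes are derived, and it tends to favour restless nights. Dilution of group differences toward the null follows only if an intervention does consolidate sleep and still spells of this length do occur. How often a sleeping child's wrist device records more than 60 minutes of zeros is not in the documents, so neither the loss of nights nor the bias can be sized. The rule is cheap to change and should be changed before any night is scored.

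**What to change.** Keep the 60-minute zero-count rule for the daytime activity data only. For nights:

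- Do not treat zero counts between logged bedtime and logged wake-up time as non-wear.
- Judge wear over that logged interval from a device-removal item added to the parent sleep log, or from a wear sensor if the device has one. This replaces the threshold of 8 h within 2200–0700.
- Still check, and exclude, nights with zero counts throughout the logged interval.
- Report the number of rejected nights by arm and time point.

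The cost is one extra log item and slightly more data handling, since parents already record bedtime and wake-up time. The main risk is that a removal parents fail to log could be scored as sleep, an error in the opposite direction. The check on all-zero nights is there to catch the worst of these, but a shorter unlogged removal would pass it.

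### Urinary aMT6s is labelled endogenous melatonin and compared across all four groups, but in the two supplemented groups at T2 it reflects endogenous plus ingested melatonin

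*Protocol article*

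**What the plan says.** Under Primary outcome measures, the second primary outcome is defined as follows: "The endogenous melatonin level of the participants, reflected by the 6-sulfatoxymelatonin (aMT6s, creatinine-adjusted morning urinary melatonin representative"). It is measured in 24-hour and first-morning urine. The Study measures section applies the measurements at T1, T2 and T3 and exempts no group. The abstract describes the same assay without the word endogenous: "Melatonin levels represented by 6-sulfoxymelatonin will be measured from the participants’ 24-h and the first morning void urinary samples".

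On exposure, the section on Intervention B states: "Participants in this intervention group will undergo a 10-week melatonin supplement intervention period". The Intervention A section says of the supplement in B and C "which will be prescribed to the participants every day". For the combination group: "Participants will receive the jogging program and supplemental melatonin dose with identical format as that in the intervention A and B". For the control group: "Participants in the control group will receive no jogging and melatonin supplement dosing activity"; these children take a placebo. The Intervention section places T2 five weeks after the start and T3 after the ten weeks.

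On analysis, Statistical methods names all four groups and says of the analysis of variance: "ANOVA) with repeated measures will be performed to compare changes in actigraphy data and endogenous melatonin level between and within groups". The mediation analysis is to "examine the mediating effect of endogenous melatonin level at T2 on the relation between physical exercise and sleep at T3". It does not say which groups enter.

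**The concern.** A urinary metabolite of melatonin does not show whether the melatonin was made by the child or swallowed. Half of the randomised children swallow it daily, and T2 lies inside the dosing period. If the plan is followed as written, a T2 rise in the melatonin or combination group would be reported as a change in endogenous melatonin when it may show only that the supplement was taken.

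Two conclusions are at stake. One is the group comparison on a primary outcome. The other is the second objective, the melatonin-mediated mechanism, because the mediator is this same marker at T2. The sleep outcomes measured by actigraphy are not touched.

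**Working it through.** **The plan's own figure.** The sample size is background only and is not disputed here. With d = 0.9, two-sided 5% alpha (sidedness assumed) and 80% power, n = 2(1.96 + 0.842)²/0.9² = 19.4, so 20 per group, as stated. The t-test version gives 20.4, so 21. Power at 20 per group is 79.2% by the t-test.

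**What the marker contains, by group and time.** This follows from the dosing and assessment sections. It rests on the premise that aMT6s is formed from melatonin of either source; no source-specific assay is described.

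| Group | T1 | T2 (week 5) | T3 |
|---|---|---|---|
| Jogging | endogenous | endogenous | endogenous |
| Melatonin | endogenous | endogenous + ingested | not determinable |
| Combination | endogenous | endogenous + ingested | not determinable |
| Placebo control | endogenous | endogenous | endogenous |

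T1 precedes dosing, and the inclusion criteria bar prior melatonin treatment. T3 cannot be classified because the protocol does not say whether dosing continues into that assessment week.

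**Illustration of the consequence.** The documents give no figure for the supplement's contribution, so it is left as an assumption, k, in units of the between-child SD of endogenous aMT6s. The other assumptions are 20 children per group, jogging raises endogenous melatonin by 0.9 SD (borrowed from the sleep effect, since none is given for aMT6s), the supplement does not change endogenous output, and ingested melatonin adds k SD with a between-child SD of 0.3k. There were 2,000 simulated trials per k.

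| k | Melatonin vs control significant | Correlation of measured with true endogenous level, supplemented groups | Power for exercise effect on aMT6s, four groups, no supplement term |
|---|---|---|---|
| 0 | 5% | 1.00 | 97% |
| 0.5 | 34% | 0.99 | 97% |
| 1 | 86% | 0.96 | 96% |
| 2 | about 100% | 0.88 | 84% |
| 5 | 100% | 0.59 | 13% |
| 10 | 100% | 0.34 | below 1% |

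The correlations can be checked by hand. Endogenous variance across the two supplemented groups is 1 + 0.9² × 0.25 = 1.2025, so the correlation is √[1.2025/(1.2025 + 0.09k²)]. At k = 5 this is √(1.2025/3.4525) = 0.59.

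**What a supplement term does.** With exercise and supplement both in the model, the average residual variance is 1 + 0.045k² and the standard error of the exercise effect (40 versus 40) is √[2(1 + 0.045k²)/40].

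- k = 2: SE 0.243, 0.9/0.243 = 3.70, power about 96%.
- k = 5: SE 0.326, 0.9/0.326 = 2.76, power about 79%.
- k = 10: SE 0.524, 0.9/0.524 = 1.72, power about 40%.

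Jogging versus control alone has SE √(2/20) = 0.316 and power 79.2%, whatever k is. The two standard errors are equal when 1 + 0.045k² = 2, that is k = √(1/0.045) = 4.7. The exercise effect is estimated without bias in each of these models under the stated assumptions. Leaving out the supplement term costs power; it does not shift this path. The path from mediator to sleep was not simulated.

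**The case against.** The strongest defence has three parts.

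First, total melatonin is a legitimate quantity in the supplemented groups. The second objective asks how all the interventions act through melatonin, the stated hypothesis expects melatonin to come from both exercise and supplement, and the abstract speaks only of melatonin levels. This stands. It supports renaming the outcome in those groups, and it is a reason not to reduce it to a mere adherence check.

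Second, the mediation text names one path, from exercise to sleep, and is silent on groups; that detail may sit in an analysis plan not shown. The sensitivity analysis gives exercise and supplement separate terms with an interaction. This also stands: the mediator is contaminated only if the melatonin or combination group enters, which the text neither states nor excludes. Likewise, not mentioning T1 covariates is no error in itself.

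Third, combination versus melatonin is a randomised comparison of jogging among children with the same melatonin prescription. It carries information on exercise, provided jogging does not alter how the supplement is handled. It would be wrong to say that the supplemented groups carry none.

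A reader might go further and infer that aMT6s in these groups measures only the supplement, that it exceeds the endogenous signal many times over, or that the three assessments run off, on and off supplement. The documents support none of these. They give no recovery or output figures and do not state dosing status at T3.

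None of this rescues the four-group comparison under the label endogenous. That rule is stated in the text, and no later analysis detail can make the T2 marker endogenous in children taking melatonin.

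**Conclusion.** The point holds for the labelling and the four-group comparison. At T2, in two of four groups (50 of the 100 children to be recruited), the primary outcome called endogenous melatonin is endogenous plus ingested melatonin, and a rise there does not show a rise in endogenous melatonin. T1 in all groups and jogging versus placebo control remain valid; T3 in the supplemented groups is undetermined.

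The size in this trial is unknown because the documents do not give the supplement's contribution. Under the stated assumptions, a contribution of 1 SD is enough to make the melatonin versus control comparison significant in 86% of trials with no endogenous effect at all. For the mediation analysis the conclusion is conditional on the supplemented groups entering. A reader might infer that the exercise mediation result would then be wrong; what was shown is a loss of power on the exercise-to-melatonin path when no supplement term is fitted.

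**What to change.** 1. Limit the endogenous melatonin comparison, and any conclusion drawn from it, to jogging versus placebo control.
2. In the melatonin and combination groups, rename aMT6s total melatonin (endogenous plus supplement) and interpret it as exposure.
3. Make jogging versus placebo control the primary exercise–melatonin–sleep mediation analysis. Any four-group version should include a supplement term and its interaction with exercise, and be labelled as total melatonin.
4. Include T1 aMT6s and T1 sleep, both already collected, as covariates in the mediation equations.

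The protocol should also state whether T3 urine in the supplemented groups is collected with dosing continuing or ended, so that T3 values can be interpreted.

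Cost: the main mediation analysis rests on 2 × 20 = 40 (the plan's completers) to 2 × 25 = 50 (recruited) children instead of 80 to 100, so its interval is wider. On the exercise-to-melatonin path, power in the illustration is 79% for the two groups, against 96% for four groups with a supplement term at k = 2; the two are about equal near k = 4.7. This is a change to analysis and wording only. No change to dose or sampling is proposed.
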